#### MFS

The MFS is designed to assess the risk of falling in the next 6 months. The main questions include “Did you have a fall last year? Has FOGQ happened in the past month? Does it take you more than 3.6 s to walk 4 m in a relaxed manner?” The total score ranges from 0 to 125, with higher scores indicating higher risks of falls.

### Adherence Promotion

Participant adherence is measured by the rate of recruitment and retention, online time, and other adherence performance. Coaches and doctors are responsible for supervising and managing the participants:

(1) Before each exercise, the attendance rate will be counted.(2) During the exercise, log-in time in the video conference and Care-PD app will be recorded, respectively. Moreover, coaches will supervise the exercise through video conference which will be recorded and reviewed subsequently.(3) Before and after the intervention, the time spent on filling online questionnaires will also be recorded.

In addition, the subjects will receive verbal encouragement and humanistic care. We plan to reward participants for following instructions to improve their adherence to the program. Immediate results from the assessment module in the application will also create a positive feedback loop that stimulates participant adherence.

### Adverse Events

Subjects need to record daily adverse events, including falls, muscle soreness, injuries, and dizziness. Once an adverse event occurs, they should contact the doctors or researchers as soon as possible and call the emergency number if necessary. To ensure that subjects complete the record of adverse events, the doctors and the researchers will verify the record every time they contact the participants.

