### Participant Timeline

As shown in Table 1, the research will be conducted according to the following timeline. First, the subjects will fill out the ADL form and the informed consent form. After evaluation and screening by administrators, persons with PD who fit the inclusion criteria will continue to complete baseline evaluation consisting of eight questionnaires. Then, they will be divided into three groups and participate in a 12-week exercise program. At the end of the program, subjects will complete the evaluation questionnaires. For the next 4 weeks, a follow-up study without exercise intervention will continue. Adverse events will be recorded from week 0 to 16. The questionnaires, same as the ones at baseline, will be filled out again at the end of week 16.

**Table 1 T1:** The time points of data collection.

		**Baseline T0**	**Intervention**	**Intervention end**	**Follow-up**	**Follow-up**
**Assessment**	**Recruitment**	**(Week 0)**	**period**	**T1**	**period**	**end T2**
			**(Week 0–12)**	**(Week 12)**	**(Week 12–16)**	**(Week 16)**
M-EDL		√		√		√
PDQ-39		√		√		√
WOQ-9		√		√		√
FOGQ		√		√		√
CSI		√		√		√
nM-EDL		√		√		√
ADL	√	√		√		√
MFS		√		√		√
Adverse events			√		√	

*“√” means the outcomes will be evaluated in this period. M-EDL, Motor Experiences of Daily Living; PDQ-39, 39-item Parkinson's disease Questionnaire; WOQ-9, The 9-item Wearing-Off Questionnaire; FOGQ, Freezing of Gait Questionnaire; CSI, Caregiver Strain Index; nM-EDL, Non-motor Experiences of Daily Living; ADL, Activities of Daily Living; MFS, Morse Fall Scale*.

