### Intervention

All subjects will take medicine according to prescriptions and record the use of medicine in the Medication Recording module (37). Exercise videos of Tai Chi and stretching exercises will be uploaded to the Exploratory Research module in advance. Each Tai Chi and stretching exercises session consists of 10 min of warm-up, 45 min of exercise, and 5 min of cool-down. The program will last for 12 weeks, with each week containing three sessions of 1-h long exercises, followed by 4 weeks of follow-up without intervention. To ensure safety, subjects will be asked to clear up the surroundings in advance with the assistance of caregivers.

In addition, WeChat and Tencent Meeting will be used for communicating with the participants. Before each intervention, Care-PD will send a notification as well as a text message to remind the participant to exercise according to schedule. During the intervention, a video conference will be initiated that the subjects then join with the camera on. The entire process of the exercise intervention will be supervised and recorded. The researchers will inform subjects on the techniques of exercise, safety precautions, and emergency measures in case of adverse events. At the end of the intervention, the researchers will remind the subjects to log in and inquire about changes in their physical and psychological conditions. The specific plan of intervention is shown in Figure 3. The detailed moves of Tai Chi and stretching exercises are presented in Table 2.

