### Control Group

The modules of the Care-PD app available to the control group are consistent with those of Tai Chi group and stretching exercises group except for training programs. The control group will have access to the Medication Recording module but not the exercise videos. After the trial, Tai Chi and stretching exercises videos will be available to all participants in the control group.

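### The completeness check on adverse-event records is triggered by staff contact, which is built into the exercise arms but not described for control, so event counts risk unequal ascertainment

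*Protocol article*

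**What the plan says.** **Capture.** The Adverse Events section sets the basic record for everyone: "Subjects need to record daily adverse events, including falls, muscle soreness, injuries, and dizziness". It also tells participants to contact doctors or researchers promptly once an event occurs. The Participant Timeline section sets the window: "Adverse events will be recorded from week 0 to 16".

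**Verification.** The same Adverse Events section adds one check, whose stated purpose is to make sure the record is complete: "the doctors and the researchers will verify the record every time they contact the participants". It gives no schedule for that contact.

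**Contact in the exercise arms.** The Intervention section describes a 12-week programme, "with each week containing three sessions of 1-h long exercises, followed by 4 weeks of follow-up without intervention". For the sessions, "During the intervention, a video conference will be initiated that the subjects then join with the camera on", and "The entire process of the exercise intervention will be supervised and recorded". At the end of the intervention, "the researchers will remind the subjects to log in and inquire about changes in their physical and psychological conditions".

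**Contact in the control arm.** The Control Group section gives this arm the same app modules apart from training: "The control group will have access to the Medication Recording module but not the exercise videos". The text describes no regular staff contact for it. The Recruitment section lets any participant approach the administrators during the intervention period, but at the participant's own initiative.

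**The concern.** The daily diary is the same in all arms, but the step meant to find what the diary missed is not. It takes place when staff are in touch with a participant, and the protocol ties regular contact to the assigned treatment. An event that a control participant forgets to enter has no described occasion on which it would come to light. The same lapse in an exercise participant may be caught at the next session. After week 12 that opportunity falls away in the exercise arms too, at the moment exercise stops.

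Falls, soreness, injuries and dizziness are the listed events. More complete recording under exercise could look like harm from home exercise, or could offset a real reduction in falls, which the Introduction and Discussion cite as a benefit of Tai Chi. A drop in recorded events after week 12 could likewise be read as an effect of stopping exercise when it partly reflects less checking.

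**Working it through.** The article states no figure on this point, so there is nothing to reproduce. The check has three parts.

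**1. Scheduled contact by arm and period**

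| Period | Tai Chi | Stretching | Control |
|---|---|---|---|
| Weeks 0–12 | 3 per week × 12 weeks = 36 sessions | 3 × 12 = 36 sessions | none described |
| Weeks 12–16 | no sessions | no sessions | none described |

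The inputs are in the Intervention and Control Group sections. The table counts sessions. It does not count verifications.

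**2. Does a session count as a verification contact?** Verification is assigned to doctors and researchers. The sections differ on whether they attend:
- Recruitment: the administrators, who include doctors and researchers, supervise exercise and act as training instructors.
- Intervention: researchers brief participants on technique, safety and emergencies, and ask about physical and psychological changes at the end of the intervention. That could mean each session or week 12.
- Adherence Promotion: coaches and doctors supervise and manage participants.
- Tai Chi Group: a Tai Chi specialist supervises remotely, with researchers not involved.
- Stretching Exercises Group: no such exclusion.

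So 36 is an upper figure. If sessions count in both exercise arms, those two arms are checked alike. If the exclusion of researchers is taken literally, verification could also differ between Tai Chi and stretching, which is the contrast in the stated hypothesis.

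**3. Possible size, on assumed capture rates.** None of the rates below is in the article. Let the true proportion with an event be p in both arms, and capture be c_E under exercise and c_C in control. Then

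apparent risk ratio = (p × c_E) / (p × c_C) = c_E / c_C.

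With c_E = 0.90:
- c_C = 0.90: ratio 1.00, no bias
- c_C = 0.80: 0.90/0.80 = 1.125, about 1.13
- c_C = 0.70: 0.90/0.70 = 1.29
- c_C = 0.50: 0.90/0.50 = 1.80

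The chance that a two-sided 5% test of two proportions, 60 against 60, shows a spurious excess under exercise is approximately Φ[(d − 1.96 × SE0)/SE1]. Here d is the observed difference, SE0 the pooled and SE1 the unpooled standard error. Example with p = 0.30 and c_C = 0.70: observed 0.27 and 0.21, d = 0.06, SE0 = √(0.24 × 0.76 × 2/60) = 0.0780, SE1 = √[(0.27 × 0.73 + 0.21 × 0.79)/60] = 0.0778, giving Φ(−1.19), about 12%.

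| True p | c_C = 0.80 | c_C = 0.70 | c_C = 0.50 |
|---|---|---|---|
| 0.20 | 5% | 9% | 24% |
| 0.30 | 6% | 12% | 36% |
| 0.50 | 8% | 20% | 63% |

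With equal capture the corresponding figure is 2.5%, one tail of the 5% test. In the other direction, at 0.90 against 0.70 a true ratio of 0.70/0.90 = 0.78 would appear as 1.00.

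**The case against.** The strongest reply is that capture is common to all arms. Every participant keeps a daily record, is told to contact staff when an event occurs, and is followed to week 16. Control has the same modules apart from training. A control participant who reports an event thereby creates a contact, and so a verification. This stands, and it limits the bias. It does not remove it, because an event that is neither entered nor reported is what the check is meant to find, and the opportunities to find it are unequal.

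A reader might infer 36 verifications against none. The article does not support that count. The staff who verify may not attend Tai Chi sessions, reminders are app notifications and text messages, and the absence of contact in control is silence in a condensed article whose intervention figure for that arm is not shown.

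A reader might also infer that the safety comparison is biased. No between-arm or between-period test of adverse events is named under Data Collection, Management, and Analysis, and adverse events are not among the primary or secondary outcomes. The questionnaire outcomes do not depend on this rule. What survives is that event counts set out by arm or period would be open to misreading, with or without a p-value.

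Finally, operational detail may sit in a fuller document. The point does not rest on missing detail, however. It rests on a stated rule that makes checking follow contact.

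**Conclusion.** The point holds as a risk. The only completeness check described follows staff contact, contact is regular in the exercise arms in weeks 0 to 12 and not described for control, and it falls in the exercise arms after week 12. Exercise-versus-control counts and exercise-period-versus-follow-up counts are therefore exposed to unequal ascertainment, most plausibly making exercise look less safe than it is.

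The size is unknown. The ratios of 1.00 to 1.80 above show the mechanism under assumed capture rates and measure nothing in this trial. Tai Chi versus stretching is largely unaffected, provided sessions in both arms count as verification contacts, which the article leaves unclear. This is a cheap improvement to safety data collection and no threat to the efficacy analysis.

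**What to change.** 1. Replace contact-triggered verification with one fixed schedule, the same in all three arms from week 0 to 16, using the same standard questions. A weekly prompt through the app's Adverse Report module would do. If the sponsor wants staff to verify in person, that contact should follow the same schedule in every arm.
2. Base any between-arm or between-period description of adverse events on what that schedule captures. List events noted only during exercise sessions separately.
3. Reconcile the Recruitment, Intervention and Tai Chi Group sections on whether doctors or researchers take part in sessions, and say whether a session is a verification contact.

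The daily record and the instruction to contact staff when an event occurs stay as they are. The app already has the reporting module and sends notifications, so the cost is the prompt, its wording and a small extra burden on participants, mainly in control. An automated prompt needs no added staff, but it does not by itself equalise staff contact, which is why the separate listing in item 2 is needed.

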### Sample Size

The calculation of sample size is based on a previous study finding a power size of 0.8 with 45 participants in each group (21). We use G^*^Power 3.1.9.7 software to calculate the number of subjects (53, 54). A sample of 180 subjects (60 subjects in each group) is required to realize the effect size dose of 0.25 with 0.05 alpha, and the drop-off rate of 30–35% will be considered. The sample calculation utilizes the analysis of variance (ANOVA) analysis of repeated measures among factors.

### Data Collection, Management, and Analysis

All personal information will be kept strictly confidential, such as age and disease progression. The results will be collected and stored in a database protected by passwords.

Data will be obtained from the Care-PD app and presented as mean ± SE. All statistical analyses will be performed in GraphPad Prism and R studio 3.6.3. Staff with rich experience will independently complete the processing and cleaning process of data. Baseline data between groups will use one-way ANOVA for continuous variables and normal distribution, Wilcoxon test for continuous variables and non-normal distribution, and chi-square test for categorical variables. Repeated-measure ANOVA is used to evaluate the efficacy of Tai Chi and stretching exercises on QoL and PD progression over 12 weeks (within-group). A mixed-model repeated-measure ANOVA is used to compare the difference between Tai Chi, stretching exercises, and the control (between-group).

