Until now, there have been few studies dedicated to home rehabilitation training based on smartphone apps for patients with PD. The Merrill R Landers team created the 9zest app, providing various types of exercise videos, ranging from aerobic exercise, resistance exercise, to yoga and balance training. Their study confirmed the feasibility and safety of app-based exercise (33). However, it lacked an evaluation program that tracks the efficacy of patients' exercise in real time. To overcome the limitations mentioned above, our team developed the Care-PD app, providing home rehabilitation training for patients with PD. Care-PD incorporates Tai Chi, stretching exercises videos, as well as the Self-Assessment module. However, randomized controlled trials on Tai Chi and stretching exercises based on the app are yet to be conducted. This study will conduct recruitment of persons with PD, exercise intervention, and outcome evaluation solely based on the Care-PD app (34).

This study aims to determine the practicability of recruiting subjects, conducting exercise intervention, and evaluating outcomes using a smartphone app only. Additionally, we will explore the effect of Tai Chi and stretching exercises on PD progression. This is the first online randomized controlled trial entirely based on a smartphone app in China. We hypothesize that compared to stretching exercises, Tai Chi is more effective in improving QoL and disease progression.

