### Participants

We will conduct online recruitment (e.g., WeChat) and post advertisements in communities and hospitals to recruit more participants. The researchers in charge of recruitment will remotely guide participants through the registration process. The subjects with PD interested in our research will sign up for the phone app.

Before enrollment, participants will be comprehensively evaluated based on the following items: (1) diagnosis certificate or recent medical records uploaded in Care-PD (Supplementary Figure 1A), (2) Activities of Daily Living (ADL) index scoring (35, 36), and (3) remote video conference evaluation conducted by professional neurologists. The video conference utilizes two cameras (the primary camera and the secondary camera) to remotely monitor the subjects' performance.

We plan to recruit 180 participants who will be divided into three groups using a 1:1:1 randomization formula: Tai Chi group, stretching exercises group, and control group. Every eligible subject will sign the informed consent form in the app (Supplementary Figure 1B).

The inclusion criteria for subjects with PD are:

(1) Diagnosis of idiopathic PD,(2) Age of 40 to 75 years with the ratio of males to females ~1–1,(3) Currently receiving pharmacologic treatment (levodopa) under stable conditions,(4) Scoring over 55 in ADL index,(5) Willingness to cooperate with treatment and sign the informed consent form.

The exclusion criteria are:

(1) Diagnosis of typical PD,(2) Inability to stand for 45 min or complete exercise training,(3) High risk of falls in the next 6 months indicated by Morse Fall Scale (MFS) (37),(4) Severe cognitive or mental disorders verified through remote video conference with the help of caregivers,(5) Inability to use a smartphone or lack of assistance from family members or caregivers to do so.

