During the COVID-19 pandemic, face-to-face assessment is risky and inconvenient. Therefore, it is necessary to build an online evaluation platform for home rehabilitation exercises. Care-PD is a home rehabilitation app, providing Tai Chi and stretching exercises videos created by professional coaches and neurologists. Patients can not only exercise under the guidance of tutorial videos but also track disease progression in the app. The most significant difference between our study and the protocol of Gao et al. (34) is that our study is entirely based on the mobile app, which integrates subject recruitment, exercise intervention, and outcome evaluation. Gao et al. introduced the platform of Care-PD in management and rehabilitation for persons with PD. Despite the lack of significant difference between Tai Chi group and the control group, they demonstrated that after 8 weeks of rehabilitation using Care-PD for Tai Chi and medicine management, both the motor and non-motor symptoms of participants improved. Thus, the Care-PD platform is a viable option for home rehabilitation.

This study will explore the effect of Tai Chi and stretching exercises on QoL, motor and non-motor symptoms for persons with PD utilizing the Care-PD app. In the future, we plan to further promote and popularize the Care-PD app among persons with PD. However, there still exists certain limits. First, the majority of PD patients are between 60 and 80 years old and cannot operate mobile phones readily. Second, it is difficult to ensure the consistency of exercise intensity and duration for every participant as exercise intervention is conducted remotely. Last, outcomes can only be assessed through online questionnaires in the app. Physical examinations that require face-to-face contact, such as the 6-Min Walk Test, Timed Up and Go test, Limits of Stability, and Functional Reach Test, cannot be performed.

Moreover, the subjects need to maintain their habitual lifestyles, physical activity, and avoid participating in other exercise programs.

In conclusion, we hope that Care-PD and its exercise and assessment features can reach more PD patients in need of home rehabilitation, ultimately improving their QoL as well as motor and non-motor symptoms. Care-PD will serve as a rehabilitation platform assisting PD patients and caregivers, as well as guides and other materials for the reference of neurologists.

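### The plan attaches efficacy to a within-group before-after ANOVA, sets a three-arm between-group ANOVA beside it, and does not say which one decides

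*Protocol article*

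**What the plan says.** The section Data Collection, Management, and Analysis gives two efficacy-related analyses in consecutive sentences. The first reads: "Repeated-measure ANOVA is used to evaluate the efficacy of Tai Chi and stretching exercises on QoL and PD progression over 12 weeks (within-group". The second reads: "A mixed-model repeated-measure ANOVA is used to compare the difference between Tai Chi, stretching exercises, and the control (between-group". The word *efficacy* occurs only in the first; the second is described only as a comparison of the arms. Neither is named as the analysis that decides.

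Three other places bear on which one is meant:

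- **Participants:** patients are "divided into three groups using a 1:1:1 randomization formula: Tai Chi group, stretching exercises group, and control group".
- **Introduction:** the hypothesis is comparative: "We hypothesize that compared to stretching exercises, Tai Chi is more effective in improving QoL and disease progression".
- **Sample Size:** "A sample of 180 subjects (60 subjects in each group) is required to realize the effect size dose of 0.25 with 0.05 alpha", calculated with a repeated-measures ANOVA described as being among factors.

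The Discussion describes earlier work on the same app: "Despite the lack of significant difference between Tai Chi group and the control group, they demonstrated that after 8 weeks of rehabilitation", symptoms had improved. It goes on to call the platform a viable option for home rehabilitation.

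**The concern.** A repeated-measures ANOVA inside one arm asks whether that arm changed over time. It does not ask whether the exercise caused the change. Several other things can move the scores here. All eight outcomes are questionnaires completed by patients or caregivers, so retest and expectation effects are possible. The exercise arms also receive reminders, live supervision and encouragement. All arms take prescribed medicine and record it in the app. A before-after test credits all of this to the exercise. The randomised comparison removes what the arms have in common.

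What is at stake is which result counts as success. If the between-group comparison is null and a within-group comparison is significant, the wording lets the second be reported as efficacy. The Discussion's account of the earlier app study shows that this pattern of results can occur on this platform, and that it can be read favourably. The within-group test also cannot address the stated hypothesis, which sets Tai Chi against stretching.

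**Working it through.** **1. The plan's own figure.** The sample size helps to show which test the authors had in mind. Inputs from Sample Size: 180 patients, 60 per arm, effect size 0.25 (read as Cohen's f), alpha 0.05, power 0.8 (from "a previous study finding a power size of 0.8 with 45 participants in each group"), and "the drop-off rate of 30–35% will be considered". The number of measurements m and the correlation rho between them are not given, so they are varied.

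For a between-factors repeated-measures ANOVA with k = 3 groups, the noncentrality is lambda = f² × N × m / (1 + (m − 1) × rho), with k − 1 and N − k degrees of freedom.

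- m = 2, rho = 0.5: N = 120 gives lambda = 0.0625 × 120 × 2 / 1.5 = 10 and 80% power. Inflated for dropout, 120/0.70 = 172 and 120/0.65 = 185; at one third, 120/(2/3) = 180.
- m = 3, rho = 0.5: N = 108, or 155-167 after dropout, which does not reach 180.
- m = 3, rho = 0.7: N = 129, or 185-199 after dropout.

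So 180 can be reproduced from a between-group test, but only with assumed m and rho. This suggests that the trial was sized on a comparison of arms. It does not settle which analysis decides efficacy.

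**2. How often the within-arm test is significant when exercise does nothing.**

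- Completers per arm, from the document: 60 × 0.65 = 39 and 60 × 0.70 = 42.
- Assumptions not in the documents: no exercise effect; the same improvement c (in SD units) in every arm; rho = 0.5 to 0.7 between baseline and week 12.
- Paired t test, two-sided 0.05, standardised change dz = c / sqrt(2 × (1 − rho)). With rho = 0.5, dz = c; with rho = 0.7, dz = c/0.775.
- For at least one of two independent exercise arms, the probability is 1 − (1 − p)².

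| Common improvement | n = 39, rho 0.5 | n = 42, rho 0.5 | n = 39, rho 0.7 | n = 42, rho 0.7 | At least one of two arms (range) |
|---|---|---|---|---|---|
| 0 SD | 5.0% | 5.0% | 5.0% | 5.0% | 9.8% |
| 0.1 SD | 9.3% | 9.7% | 12.3% | 12.9% | 18-24% |
| 0.2 SD | 23.0% | 24.4% | 34.9% | 37.2% | 41-61% |
| 0.3 SD | 44.7% | 47.6% | 65.4% | 68.8% | 69-90% |

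The benchmark for the last column is 1 − 0.95² = 9.75%, about 10%, not 5%.

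**3. The same setting with ANOVA.** A simulation with 4,000 runs used the one-arm repeated-measures ANOVA itself, at 60 per arm without dropout. For c = 0.1, 0.2 and 0.3 SD, a given arm was significant in about 11%, 33% and 66% of trials with rho = 0.5, and in 16%, 51% and 87% with rho = 0.7. In the same runs the three-arm group-by-time test was significant in about 5% throughout. That is expected: equal change in every arm is exactly its null hypothesis, so the size of the common change does not affect it.

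**The case against.** The strongest objection is that the sentence on within-group analysis does not stand alone. The next sentence brings the control arm into a three-group comparison, the hypothesis is comparative, and the sample size appears to rest on a between-group test. All of this is correct. A reader might infer from the first sentence that the control arm goes unused, or that following the plan would necessarily declare both exercises effective. The documents support neither reading: the control arm is analysed, and no rule makes the within-group result sufficient.

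It can also be said that the choice between two stated analyses belongs in the statistical analysis plan, which is not shown. That would answer a silence. Here, however, the article itself gives the efficacy role to the within-group test, and that assignment is open to correction.

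Two further objections stand in part. The Discussion passage concerns a different study and openly reports its lack of a between-group difference; it shows a risk of misreading, not how this trial will be analysed. The percentages in the working are the power to detect a real within-arm change. They become false efficacy claims only if the within-group result is taken as decisive. Stable levodopa treatment at entry and medication recording in all arms limit one source of common change, but do not remove retest, expectation or attention effects.

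Finally, reporting a within-arm change is not an error in itself. The defect lies in the role it is given.

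**Conclusion.** The point holds in this form: the plan labels a non-randomised before-after test as the evaluation of efficacy, places the randomised comparison beside it, and does not say which governs. A before-after improvement without any difference from control could then be reported as efficacy.

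Under the assumed common improvements of 0.1 to 0.3 SD, a given exercise arm would be significant in roughly 9% to 69% of trials when exercise does nothing, and at least one of the two in roughly 18% to 90%. The lower end is modest, so the size depends heavily on how much all arms improve together, which the documents do not let one estimate. The direction does not depend on it: any common change raises the within-arm rate above 5% and leaves the group-by-time test at about 5%. Because the wording affects which result counts as success, it should be settled before the data are analysed.

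**What to change.** In Data Collection, Management, and Analysis, move the word *efficacy* from the within-group sentence to the between-group sentence. Add that efficacy will be concluded only from between-arm differences in change from baseline to week 12: Tai Chi minus stretching, which is the stated hypothesis, and each exercise minus control. Describe within-arm change as means with 95% confidence intervals that do not support an efficacy claim.

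The change takes about two sentences and needs no further patients, visits or data, since the between-group model is already planned. The price is that a before-after improvement can no longer serve as a positive result by itself.

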#### The 39-Item Parkinson's Disease Questionnaire

The PDQ-39 is a 39-item self-report questionnaire, which assesses how often PD patients experience difficulties across eight quality of life dimensions including mobility, activities of daily living, emotional well-being, and stigma, social support, cognition, communication, and bodily discomfort (41). The questionnaire uses a 5-point ordinal scoring system (42) with each dimension total score ranging from 0 to 100, where lower scores represent better QoL (43).

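### The between-group repeated-measures ANOVA has no baseline covariate and names neither the tested term nor the visits; if it is the group main effect that its label and sizing suggest, it dilutes the week-12 effect.

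*Protocol article*

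**What the plan says.** The analysis section of the protocol article (Data Collection, Management, and Analysis) gives two efficacy analyses. One is a repeated-measures ANOVA of the exercise effect "on QoL and PD progression over 12 weeks (within-group"). The other compares the arms: "A mixed-model repeated-measure ANOVA is used to compare the difference between Tai Chi, stretching exercises, and the control (between-group"). Neither sentence names a baseline covariate, the model term to be tested or a primary visit, and the between-arm sentence does not list the visits that enter.

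Under Participant Timeline, the questionnaires are completed at baseline, week 12 and week 16. Baseline comes before division into groups, and weeks 12 to 16 are without exercise intervention.

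Under Sample Size, "A sample of 180 subjects (60 subjects in each group") "is required to realize the effect size dose of 0.25 with 0.05 alpha", with 30–35% loss considered. A power of 0.8 appears through "a previous study finding a power size of 0.8 with 45 participants in each group". The method is given as follows: "The sample calculation utilizes the analysis of variance (ANOVA) analysis of repeated measures among factors".

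The Introduction hypothesises that Tai Chi is more effective than stretching for quality of life and disease progression.

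For baseline comparisons across the three arms, the plan uses one-way ANOVA, or a "Wilcoxon test for continuous variables and non-normal distribution".

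**The concern.** In a repeated-measures ANOVA without a baseline covariate, the baseline score ordinarily sits in the outcome as one level of time. The group main effect of such a model compares arm means averaged over all visits entered. Baseline precedes assignment, so its expected between-arm difference is zero and including it pulls the average towards zero. Week 16 comes after training has stopped, so it may pull the average down further.

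Two features point to this term: the between-group label on the analysis, and the among-factors wording of the sizing, which reads as the between-factors option for repeated measures. If the main effect is the test, the trial could miss an effect at the end of training that its sample size can otherwise detect. The baseline score, already collected from everyone, would also add noise to the comparison when it could reduce it.

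**Working it through.** **Inputs from the article.** Three arms at 1:1:1, total 180, effect size 0.25 (read as Cohen's f), alpha 0.05, power 0.8, loss 30–35%. Participants remaining: 180 × 0.65 = 117 to 180 × 0.70 = 126.

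**Assumptions not in the article.** Number of visits m, correlation ρ between visits, compound symmetry, the share r of the week-12 effect kept at week 16, and f = 0.25 taken as the week-12 effect.

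**Step 1: reproduce 180.** For the between-factors test, λ = f²·N·m / (1 + (m − 1)ρ), with 2 and N − 3 degrees of freedom.
- m = 2, ρ = 0.5: N = 120, and 120 / (1 − 1/3) = 180.
- m = 3, ρ = 0.6: N = 117, and 117 / 0.65 = 180.
- m = 3, ρ = 0.5: N = 108, giving 155–167 after loss, which does not reach 180.
- Group-by-time option, ρ = 0.5: N = 36–42, giving 52–65 after loss.

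Of these two repeated-measures options, only the between-factors one recovers 180. It does so with either two or three visits, so the sizing does not show which visits were meant.

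**Step 2: the group main effect.** Over three visits the averaged effect is k = (0 + 1 + r)/3 of the week-12 effect, that is 2/3, 1/2 or 1/3 for r = 1, 0.5 or 0. The variance of a person's mean, relative to one visit, is (1 + 2ρ)/3. Hence λ = N·f²·k² / ((1 + 2ρ)/3). For baseline and week 12 only, k = 1/2 and the variance is (1 + ρ)/2. For baseline-adjusted week 12, λ = N·f² / (1 − ρ²), with N − 4 error degrees of freedom.

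At ρ = 0.5 and N = 120, N·f² = 7.5:

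| Test | λ at N = 120 | Power, N = 117–126 |
|---|---|---|
| Main effect, 3 visits, r = 1 | 7.5 × 0.444 / 0.667 = 5.0 | 0.48–0.51 |
| Main effect, 3 visits, r = 0.5 | 7.5 × 0.25 / 0.667 = 2.81 | 0.29–0.31 |
| Main effect, 3 visits, r = 0 | 7.5 × 0.111 / 0.667 = 1.25 | 0.15–0.16 |
| Main effect, baseline and week 12 | 7.5 × 0.25 / 0.75 = 2.5 | 0.26–0.28 |
| Week 12, baseline-adjusted | 7.5 / 0.75 = 10.0 | 0.79–0.83 |

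A higher correlation widens the gap: at ρ = 0.7 and r = 1 the powers are 0.41–0.44 against 0.93–0.95.

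**Step 3: the group-by-time term.** λ = N·f²·S / (1 − ρ), where S is the sum of squared deviations of (0, 1, r) about their mean, with 4 and 2(N − 3) degrees of freedom. At N = 120 and ρ = 0.5:
- r = 1 or 0: S = 2/3, λ = 10, power 0.71.
- r = 0.5: S = 1/2, λ = 7.5, power 0.56.
- Baseline and week 12 only: power 0.68.

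Baseline-adjusted week 12 has 0.80. At ρ = 0.8 the interaction has 0.95–0.99 against 0.99.

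**Step 4: the pairwise contrast of the hypothesis.** With f = 0.25, the Tai Chi minus stretching difference is 0.25 × √1.5 = 0.306 SD if stretching lies midway between Tai Chi and control, and 0.25 × 3/√2 = 0.530 SD if only Tai Chi differs. The noncentrality is (difference / √(1 − ρ²)) × √(n/2). At ρ = 0.5 and n = 39–42 per arm, power at two-sided 0.05 is about 0.34–0.36 and 0.76–0.80 respectively. At 0.025 it is 0.24–0.26 and 0.67–0.70.

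**The case against.** A reader might infer that the plan definitely averages baseline with weeks 12 and 16. The article does not say so. A mixed ANOVA also contains a group-by-time term, an ordinary choice for comparing arms over time. Under it nothing is averaged and baseline serves as the reference for change. What remains is a loss of efficiency, moderate at ρ = 0.5 and negligible at ρ = 0.8. Week 16 is the least supported part, since the within-group sentence stops at 12 weeks and 180 can be reproduced with two visits. Leaving week 16 out does not rescue the main effect, however: with baseline and week 12 only, power is 0.26–0.28.

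The size of the loss also depends on reading 0.25 as the week-12 effect, which the Sample Size section does not state. If 0.25 is the averaged effect, power with 117–126 analysed is 0.84–0.87 (three visits, ρ = 0.5) and the shortfall disappears. The week-12 effect would then have to be larger: 0.25 / (2/3) = 0.375 with full persistence and 0.25 / (1/2) = 0.5 with half. That objection stands as a limit on the power figures, not on the dilution.

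Three further inferences are not supported. The first is that anyone with a missing visit is dropped; this holds only for a classical implementation, and the article says mixed-model and names R. The second is that PDQ-39 will be tested as eight separate outcomes; the article gives the score range ("with each dimension total score ranging from 0 to 100") but announces no such tests. The third is that multiplicity is mishandled. Score derivation, missing data and multiplicity are commonly left to the full protocol or analysis plan. The choice of test and its sizing family are different, because the article fixes and publishes them.

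**Conclusion.** The point holds in conditional form. The article commits to a repeated-measures ANOVA without baseline adjustment, and its label and its sizing both suggest the group main effect. If that is the test, it carries about one third to two thirds of the week-12 effect over three visits, or half over baseline and week 12. Power then falls to roughly 0.15–0.51, depending on persistence and visits, against 0.79–0.83 for a baseline-adjusted week-12 comparison. These figures rest on f = 0.25 at week 12, compound symmetry, ρ = 0.5 and 117–126 analysed. If group-by-time is the test, the loss is 0.56–0.71 against 0.80 at ρ = 0.5 and N = 120, close to nothing at ρ = 0.8, and the sizing then does not match the analysis. Under either reading, adjusting for baseline at week 12 helps or does no harm.

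A minor slip is separate: a Wilcoxon test does not compare three arms. It affects only the baseline table.

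**What to change.** In Data Collection, Management, and Analysis, replace the between-group sentence with a linear mixed model:
- Outcomes are the week-12 and week-16 scores. Terms are baseline score, group, visit and group-by-visit.
- All randomised participants with at least one post-baseline score are included.
- The three-group comparison at week 12 is the main test.
- Tai Chi minus stretching at week 12, the hypothesis in the Introduction, is reported as a named contrast with its own power stated.

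In Sample Size, align the method sentence with this test and state the assumed correlation. At ρ = 0.5 the baseline-adjusted comparison needs 120 analysed, or 172–185 after 30–35% loss, so 180 is about right.

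For the baseline table, use a Kruskal-Wallis test or, more simply, descriptive statistics without tests.

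The cost is wording; R is already named. The downside is that week 16 becomes secondary. Making the pairwise contrast the sole primary test would be a further step with a real power cost (Step 4), so it should not be adopted without stating that cost.
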